### Experimental plan

The study was planned as a Simon optimal two-stage design [65] (Fig. 1), under the hypothesis that propranolol 0.2% eye micro-drops treatment decreases the incidence of ROP progression to stage 2 or 3 with plus by at least 50%. From a first analysis of the historical cohort of neonates the incidence was found to be 19%. A second and deeper analysis showed that the incidence was likely somewhat higher (24.5%) (Table 2). The study size adopted is based on the first and more conservative estimate. Therefore, considering an alpha error of 0.05 and a power of 80%, the treatment should be considered failed if:-at least 6 cases of failure (a progression of ROP to stage 2 with plus or 3 with plus) is observed in the first 37 newborns enrolled;-at least 13 out of 96 newborns enrolled show a treatment failure (a progression of ROP to stage 2 with plus or 3 with plus).

**Fig. 1 Fig1:**
[figure not shown]
Simon optimal two-stage design for phase II clinical trials

At the end of the study, if the overall cases of failure are less than 13 out of 96 newborns, the treatment with propranolol 0.2% eye drops will be considered effective in decreasing the rate of ROP progression to stage 2 or 3 with plus.

Additionally, considering the serious adverse effects observed in newborns receiving oral propranolol with plasma concentrations around 20 ng/mL, this value is currently considered a sort of safe cut-off value [55]. For this reason, if the mean propranolol plasma concentration will be less than 20 ng/ml, as expected, the treatment with propranolol eye drops should be considered safe, being unable to cause high plasma levels of propranolol.

The 96 preterm newborns will be enrolled approximately in 2–3 years. The enrokllment will be competitive: the individual centers participating in the trial will not have a predetermined number of patients to recruit, but they will compete with each other to recruit all expected patients. The trial will be completed when the last newborn enrolled has completed the treatment schedule or achieved final retinal vascularization.

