#### Efficacy and safety of oral propranolol

The studies in the OIR model provided a considerable amount of results which strongly indicate that β2-AR blockade may play a significant action against hypoxia-induced retinal neovascularization. This evidence prompted an interest in exploring the possibility that the administration of propranolol may not only be used to treat IH but also be of help in the treatment of ROP. A randomized controlled trial [56] was performed to verify the efficacy and safety of oral propranolol in preterm newborns (GA < 32 weeks) with ROP stage 2 without plus in zone II [57]. Oral propranolol significantly decreased ROP progression to both stage 3 and stage 3 with plus, and none of treated newborns progressed to stage 4. The number of newborns who underwent laser photocoagulation or bevacizumab administration was significantly lower in the treated group [56]. These data are consistent with those reported by other authors [58–60]. Despite propranolol being generally safe and well tolerated in infancy, serious adverse events have been reported in unstable preterm newborns, mainly in conjunction with other conditions, such as sepsis, anesthesia or tracheal stimulation [56]. In these patients receiving the lower dose of 1 mg/kg/day, mean propranolol plasma concentration was around 20 ng/mL. Considering that pharmacological effects of β-blockers are usually related to the plasma concentrations, it appears prudent to avoid in future clinical trials propranolol concentrations higher than 20 ng/mL, that was considered a sort of safe cut-off value [56]. Although propranolol is effective in counteracting ROP progression [56, 58–60], the incidence of adverse events indicates that systemic administration is not sufficiently safe in preterm newborns [56]. Recently, also prophylactic propranolol administered on seventh day of life showed a decreasing trend in the incidence of ROP, need for laser therapy, and treatment with anti-VEGF [61].

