### Primary endpoint

-Number of infants who progress from ROP Stage 1 in zone II or III, without plus to Stage 2 with plus or Stage 3 with plus.-Analysis of propranolol plasma concentration at the steady state (on the tenth day of treatment).

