### Secondary endpoint

-Number of infants who progress to Stage 2 without plus ROP.-Number of infants who progress to Stage 3 without plus ROP.-Number of infants who progress to Stage 4 or 5 ROP with total or partial retinal detachment.-Number of infants who need vitrectomy.-Number of adverse events due to propranolol eye drops treatment.

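### The drops are to be called safe on the group mean day-10 plasma level alone, which shows neither individual exposure nor local tolerability and cannot be changed by adverse events

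*Protocol article*

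**What the plan says.** Safety is half of the primary objective. The second primary endpoint is the propranolol plasma concentration at steady state on day 10. Under Experimental plan, in the text after Fig. 1, the article turns this endpoint into a decision: "if the mean propranolol plasma concentration will be less than 20 ng/ml, as expected, the treatment with propranolol eye drops should be considered safe". The reason given is that the drops would then be shown as "being unable to cause high plasma levels of propranolol".

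The same paragraph explains the cut-off by "considering the serious adverse effects observed in newborns receiving oral propranolol with plasma concentrations around 20 ng/mL". The Background section on oral propranolol gives its origin: "In these patients receiving the lower dose of 1 mg/kg/day, mean propranolol plasma concentration was around 20 ng/mL". It adds that "it appears prudent to avoid in future clinical trials propranolol concentrations higher than 20 ng/mL" and concludes that "the incidence of adverse events indicates that systemic administration is not sufficiently safe in preterm newborns".

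Adverse events appear under Secondary endpoint as "Number of adverse events due to propranolol eye drops treatment", with no threshold and no link to the safety decision. Stop criteria and dose changes names bradycardia, bronchospasm, severe hypotension and severe local signs as severe events. When one is due to the drops, treatment stops and the infant leaves the study. After a first adverse event the study may be restarted at a reduced dosage in a new population. Data collection methods schedules four concentration measurements on day 10: before dosing and 2, 4 and 6 hours after.

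**The concern.** The rule uses one summary number to answer a question that this number cannot answer alone.

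- **Individuals.** A mean below 20 ng/mL is compatible with some infants above it, so the stated inference about high plasma levels does not follow from the mean.
- **Local reactions.** Severe local signs are among the named severe events. A plasma level carries no information about them.
- **Observed harm.** No number of adverse events can alter the verdict as written. The events counted are also only those judged due to the drug, in an open-label trial without a control arm.
- **Missing infants.** An infant withdrawn for a severe event before day 10 may contribute no value to the mean, so the mean may omit the infants who matter most.
- **Uncertainty.** The rule uses a point estimate without a confidence limit and does not say which of the four day-10 values form the mean.

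At stake is an unsound conclusion on half of the primary objective in preterm newborns.

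**Working it through.** **The plan's own figures.** The only sized quantity is the efficacy design. With failure rates of 0.19 (null) and 0.095 (half of it), continuing on at most 5 failures in 37 and succeeding on at most 12 in 96 gives an exact one-sided alpha of 0.0493 and power of 0.802. A full search returns the same design as the Simon optimum. The efficacy plan therefore reproduces and is not affected by this point. No error rate or precision is stated for the safety rule.

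**Inputs for the safety rule.** The cut-off of 20 ng/mL and n = 96 (37 at stage 1) come from Experimental plan. The article gives neither the expected mean nor the between-infant spread, so both are assumptions shown over a range: mean m of 5, 10, 15 or 18 ng/mL, coefficient of variation (CV) 0.5 to 1.0, log-normal levels.

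**Share of infants above 20 ng/mL.** With σ² = ln(1 + CV²) and μ = ln(m) − σ²/2, the share is 1 − Φ[(ln 20 − μ)/σ].

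Example, m = 15 and CV = 0.5: σ² = ln 1.25 = 0.2231, σ = 0.4724, μ = 2.7081 − 0.1116 = 2.5965, z = (2.9957 − 2.5965)/0.4724 = 0.845, share = 0.199, or 19.1 of 96.

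| Mean (ng/mL) | CV 0.5 | CV 0.75 | CV 1.0 | Expected number of 96 | Passes the rule? |
|---|---|---|---|---|---|
| 5 | 0.1% | 0.8% | 1.9% | 0.1–1.8 | yes |
| 10 | 4.4% | 8.5% | 10.6% | 4.2–10.2 | yes |
| 15 | 19.9% | 22.2% | 22.3% | 19.1–21.4 | yes |
| 18 | 32.3% | 31.1% | 29.4% | 28.2–31.0 | yes |

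**Chance of passing when the true mean is at or above the cut-off.** Simulation from the same model (40,000 runs, CV 0.5–1.0): at a true mean of 20 ng/mL the observed mean falls below 20 with probability 0.50–0.54 (n = 96 or 37). At a true mean of 22 the probability is 0.03–0.19 for n = 96 and 0.13–0.31 for n = 37.

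**Would a confidence limit on the mean be enough?** The one-sided 95% upper limit is m + t × m × CV/√n, with t = 1.661 for n = 96. For m = 15 it is 15 + 1.661 × 15 × 0.5/√96 = 16.3 at CV 0.5 and 17.5 at CV 1.0. Both are below 20, although about a fifth of infants would be above it. A limit on the mean repairs the error control but not the step from group to individual.

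**What events can show.** With no severe event among n infants, the one-sided 95% upper limit for the true rate is 1 − 0.05^(1/n): 3.1% for n = 96 and 7.8% for n = 37. This bound follows from the sample size, not from the rule, but it is the precision that a safety statement should carry.

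**The case against.** The strongest defence is that the sentence gives its own narrow reason, low systemic exposure, and can be read as a statement about that only. The trial does not neglect safety: it plans continuous haemodynamic and respiratory monitoring, weekly blood tests, electrocardiogram and echocardiogram, eye examinations for local reactions, individual stopping and pharmacovigilance reporting. All this is true. A reader might infer from the rule that the trial ignores adverse events, and the article does not support that. What stands is that none of this information enters the stated conclusion of safety.

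A reader might also infer that the cut-off is a level shown to harm infants, so that a mean just below it indicates danger. The article does not support this either. It reports 20 ng/mL as a group mean and says the oral events arose mainly alongside conditions such as sepsis, anaesthesia or tracheal stimulation. It gives no individual levels at the time of the events. Comparing a mean with a mean is like with like; the fault lies in what is concluded from the comparison.

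Nor do the documents imply that a large share of infants will exceed 20 ng/mL. Levels with the 0.1% drops are reported as consistently below the cut-off, and a low mean leaves few infants above it. Yet the present trial raises both dosage and concentration, so the earlier levels do not settle the matter.

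Finally, intervals and event tables are commonly left to an analysis plan. That answers any complaint about missing tables. It does not answer a decision rule that the article itself spells out with threshold and rationale.

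**Conclusion.** The point holds as a should-fix. As written, the safety conclusion follows from a point estimate of the group mean and from nothing else. It does not support the claim about high plasma levels in individual infants, is silent on local reactions, cannot respond to observed events, and may leave out infants withdrawn before day 10.

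The size of the individual-exposure gap is unknown: negligible if the true mean is near 5 ng/mL, and about a fifth to a third of infants if it lies between 15 and 18. These figures rest on an assumed log-normal distribution and CV of 50–100%. The other defects follow from the text and need no such assumption. Data collection, sample size and the efficacy decision are not touched.

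**What to change.** 1. Reword the sentence in Experimental plan so that the concentration result supports only a statement on systemic exposure. Name which of the four day-10 values are used. Report the mean with its confidence limit, and the number and proportion of infants with any value at or above 20 ng/mL with an exact interval. State how many treated infants have no day-10 value and why.
2. Base the safety conclusion jointly on that exposure result and on the per-infant incidence, with exact confidence interval, of the severe events named under Stop criteria and dose changes. The denominator is all infants who received any dose, including those later excluded. Show the incidence both overall and by attribution: attribution is a judgement made in an uncontrolled trial, and the overall count alone is hard to read in infants with so much background illness.
3. Reconcile the safety wording with the stop and restart text, so that the reader knows what conclusion on safety is possible after a severe event or a restart. Which clinical rule applies is for the sponsor to decide.

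The cost is wording and analysis only, since the samples and events are already to be collected. A conclusion of safety becomes slightly harder to reach.

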### Modification

#### Stop criteria and dose changes

Considering that unstable newborns (i.e. after anesthesia induction) have shown a high risk of adverse events (hypotension and bradycardia) due to propranolol administration, whenever surgery and/or anesthesia are indicated, the discontinuation of the propranolol eye micro-drops treatment is recommended at least 24 h before.

Newborns in whom propranolol administration will be temporarily suspended for more than two doses, with the exception of a temporary suspension before surgery will be excluded from the study.

In the case of a severe adverse event (bradycardia, bronchospasm, severe hypotension or severe local signs) due to propranolol eye micro-drops therapy, the treatment will be promptly stopped and the newborn will be excluded from the study. The concentration of propranolol will be measured on dried blood spots to verify the relationship between the adverse event that occurred and the plasmatic levels of propranolol. Moreover, after the first adverse event, the study could be restarted reducing the propranolol eye drops dosage to two micro-drops of 6 μL 0.2% propranolol solution administered four times daily in each eye. An additional enrolment phase will be opened and will be based on a new study population not including newborns previously treated.

Similarly, the study could be restarted increasing the concentration of propranolol eye drops solution up to 0.3% in case of treatment failure in terms of efficacy during the first stage of the study, if plasma propranolol concentrations are below the cut off of 20 ng/ml.

The outcomes of infants who develop adverse effects to propranolol will be reported to Pharmacovigilance Center and then published.

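### A group mean below 20 ng/mL cannot by itself support calling the drops safe or unable to cause high plasma levels

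*Protocol article*

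**What the plan says.** The rule is in the protocol article, Experimental plan, in the text after Fig. 1: "if the mean propranolol plasma concentration will be less than 20 ng/ml, as expected, the treatment with propranolol eye drops should be considered safe". The sentence ends with the reason "being unable to cause high plasma levels of propranolol". The threshold is introduced with the words "considering the serious adverse effects observed in newborns receiving oral propranolol with plasma concentrations around 20 ng/mL".

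Other places bear on it:

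- **Efficacy and safety of oral propranolol** gives about 20 ng/mL as the mean level in infants on the lower oral dose of 1 mg/kg/day, and concludes that "it appears prudent to avoid in future clinical trials propranolol concentrations higher than 20 ng/mL".
- **Primary endpoint** lists the day-10 steady-state concentration beside ROP progression.
- **Data collection methods** plans four day-10 samples per infant: before the dose and 2, 4 and 6 h after it.
- **Secondary endpoint** lists "Number of adverse events due to propranolol eye drops treatment", with no limit attached and no link to the safety rule.
- **Stop criteria and dose changes** uses the threshold once, for a possible restart at 0.3% after efficacy failure: "if plasma propranolol concentrations are below the cut off of 20 ng/ml". It also stops treatment and excludes the infant after a severe adverse event attributed to the drops, and has that infant's level measured.

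**The concern.** The rule moves from an average to a statement about what the drops can do in any infant. A group can average well below 20 ng/mL while some of its members are above it, so a low mean does not show that high levels cannot occur.

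The threshold is also placed where the protocol reports harm. About 20 ng/mL is the mean exposure on oral propranolol, a treatment the article itself judges not safe enough. A trial mean of 19.9 ng/mL would reproduce that exposure and still pass.

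Nothing clinical can overturn the verdict, because adverse events are not part of the rule. An infant stopped and excluded for a severe event before day 10 contributes no day-10 value, so the mean can omit an infant who tolerated the drug badly.

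At stake is the conclusion on a primary endpoint: the trial could report the drops as safe when its own data do not show it.

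**Working it through.** **What the plan computes.** The 20 ng/mL rule has no sample size or error rate of its own. The 96 infants come from the efficacy design, which reproduces. With failure rates of 19% and 9.5%, and continuation on at most 5 of 37 and at most 12 of 96, the exact alpha is 0.049 and the power 0.802.

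**Step 1: does a mean below 20 bound individuals?** No distribution is needed. If 72 infants were at 5 ng/mL and 24 at 25 ng/mL, the mean would be (360 + 600)/96 = 10. The rule is met with a quarter of infants above 20. This shows the logic and is not a forecast.

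**Step 2: what mean is plausible?**

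- Dose: 3 micro-drops × 2 eyes × 4 times = 24 micro-drops per day. The Intervention section prints 6 μg per micro-drop, giving 0.144 mg/day. A 6 μL drop of a 0.2% solution holds 12 μg, giving 0.288 mg/day. Both are carried forward.
- Assumed scaling: level proportional to dose per kg, with oral bioavailability, anchored at 20 ng/mL for 1 mg/kg/day. So m = 20 × (mg/day ÷ kg).
- Weight: Table 1 gives a mean birth weight of 843 g, gestational age of 26.7 weeks and postmenstrual age at diagnosis of 34.2 weeks (infants with stage 1 at first visit). Treatment starts at diagnosis, about 34.2 − 26.7 = 7.5 weeks after birth, so birth weight is too low. The article gives no weight at treatment; 1.5–2 times birth weight is assumed.

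| Weight | m at 0.144 mg/day | m at 0.288 mg/day |
|---|---|---|
| 0.843 kg (birth) | 3.42 | 6.83 |
| 1.5 × birth | 2.28 | 4.56 |
| 2 × birth | 1.71 | 3.42 |

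**Step 3: share above 20.** The article gives no SD, so a log-normal with CV c of 0.5, 0.8 or 1.0 is assumed: s² = ln(1 + c²), μ = ln m − s²/2, P = 1 − Φ((ln 20 − μ)/s).

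Worked case, m = 10 and c = 0.5: s² = 0.223, s = 0.472, μ = 2.303 − 0.112 = 2.191, z = (2.996 − 2.191)/0.472 = 1.70, P = 4.4%, or 4.2 of 96.

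| Mean m (ng/mL) | Expected number of 96 above 20, at CV 50%, 80%, 100% |
|---|---|
| 1.71 | 0.0, 0.0, 0.0 |
| 2.28 | 0.0, 0.0, 0.1 |
| 3.42 | 0.0, 0.2, 0.5 |
| 4.56 | 0.0, 0.7, 1.4 |
| 6.83 (birth weight, higher dose) | 0.6, 2.9, 4.2 |
| 10 | 4.2, 8.7, 10.2 |
| 15 | 19.1, 21.4, 21.4 |
| 19.9 | 38.6, 34.5, 32.3 |

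The rows from 1.71 to 4.56 are the plausible range. The last three show only what the rule would accept. The model uses one level per infant; counting the highest of four samples would raise the figures somewhat.

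**Step 4: would a count be informative?** Clopper–Pearson 95% intervals: 0 of 96 gives 0–3.8%; 1 of 96 gives 0.0–5.7%; 4 of 96 gives 1.1–10.3%. A count of zero would support a bounded statement about high levels, which the mean cannot.

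**The case against.** The strongest reply is that 20 ng/mL is itself a group mean, so comparing mean with mean is like with like, and the documents establish no toxic limit for an individual infant. That stands. The protocol calls the figure only a sort of cut-off, and its advice to avoid higher concentrations does not say whether it means individuals or averages. But the reply defends the comparison, not the conclusion drawn from it. A mean comparable to the oral one gives no ground for the word safe, and the final clause goes beyond any mean.

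It also stands that exceedance is unlikely at the planned dose. Nasolacrimal compression is meant to lower absorption, and levels with the 0.1% drops were well below oral ones. The means of 15 to 19.9 in the table are more than three times the highest plausible estimate of 4.56. They show how permissive the rule is.

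Four stronger readings are tempting, and the documents do not support them:

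- **Infants above 20 should have their dose cut.** Under the log-normal model, 34–40% of a group averaging 19.9 lie above 20, so crossing it does not by itself mark an infant at risk. The two-micro-drop dose in the protocol is a study-level restart dose for a new population; using it within the 96 would mix two regimens in one single-arm test.
- **Infants are unprotected.** The exclusions, the pause before anesthesia, three weeks of continuous monitoring and stopping for severe events all remain, and the study may restart at a lower dose after a first adverse event. That nothing is done about a high day-10 level cannot be inferred from a condensed article's silence.
- **The rule is weaker than the one in the 0.1% trial.** Levels consistently below 20 are reported as that trial's result; its decision rule is not given.
- **Proportions and maxima are missing from the plan.** Such summaries may be in an analysis plan not shown. The point is the rule that the article does state.

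**Conclusion.** The point holds for the safety rule and its closing clause. As written, a mean below 20 ng/mL is sufficient to call the drops safe, with no margin below the oral exposure, no use of individual levels and no use of adverse events. The logical defect rests on no assumption.

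Its practical size does. Under linear scaling from oral dosing, equal bioavailability, 1.5–2 times birth weight and a log-normal CV of 50–100%, about 0–1 of 96 infants would exceed 20. The same spread would let the rule pass with about 4–10 of 96 above 20 at a mean of 10, and about 19–21 at a mean of 15. A wrong conclusion is therefore unlikely if exposure is as expected, but the rule would not detect it if exposure were higher. It should be changed, because it settles the conclusion on a primary endpoint and the correction is nearly free.

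**What to change.** In Experimental plan, replace the mean-only rule:

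1. Do not call the treatment safe on the mean alone.
2. Alongside the mean, report the number and proportion of infants with any day-10 sample above 20 ng/mL, with an exact 95% CI, and the maximum.
3. Base the safety conclusion on these results together with the adverse events already counted as a secondary endpoint. Include infants stopped before day 10, with the reason and any level measured after the event.
4. Delete the clause saying the drops cannot cause high plasma levels, or make it conditional on the individual results.

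No individual dose-reduction rule is proposed.

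Cost: the samples and the adverse-event count are already planned, so only the wording and the reporting change, with no extra infants or blood draws. The downside is that the safety statement may come out less favourable than a mean alone would give.
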